## Abstract

**Background:**

Emotional disorders (depression and anxiety disorders) are highly prevalent mental health problems. Although evidence showing the effectiveness of disorder-specific treatments exists, high comorbidity rates among emotional disorders limit the utility of these protocols. This has led some researchers to focus their interest on transdiagnostic interventions, a treatment perspective that might be more widely effective across these disorders. Also, the current way of delivering treatments makes it difficult provide assistance to all of the population in need. The use of the Internet in the delivery of evidence-based treatments may help to disseminate treatments among the population. In this study, we aim to test the effectiveness of EmotionRegulation, a new transdiagnostic Internet-based protocol for unipolar mood disorders, five anxiety disorders (panic disorder, agoraphobia, social anxiety disorder, generalized anxiety disorder and anxiety disorder not otherwise specified), and obsessive-compulsive disorder in comparison to treatment as usual as provided in Spanish public specialized mental health care. We will also study its potential impact on basic temperament dimensions (neuroticism/behavioral inhibition and extraversion/behavioral activation). Expectations and opinions of patients about this protocol will also be studied.

**Methods/Design:**

The study is a randomized controlled trial. 200 participants recruited in specialized care will be allocated to one of two treatment conditions: a) EmotionRegulation or b) treatment as usual. Primary outcome measures will be the BAI and the BDI-II. Secondary outcomes will include a specific measure of the principal disorder, and measures of neuroticism/behavioral inhibition and extraversion/behavioral activation. Patients will be assessed at baseline, post-treatment, and 3- and 12-month follow-ups. Intention to treat and per protocol analyses will be performed.

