### Randomization and blinding

Patients will be randomly allocated in a 1:1 ratio to either of the two groups (EmotionRegulation or TAU) using a computer-generated random number sequence. The Epidat 4.1 program will be used to generate this sequence. The allocation will be carried out by an independent researcher who will be unaware of the characteristics of the study. The sequence will be concealed until interventions are assigned. Patients will agree to participate before the random allocation and without knowing to which treatment they will be allocated. Study researchers conducting psychological assessments (that is, diagnostic interviews) throughout the entire study will be masked to the participants' treatment conditions and unaware of the treatment group to which the patient belongs. For ethical and practical reasons, participants will not be blind to the treatment conditions.

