#### Sample size

The data from an RCT using the UP yielded between-group effect sizes of 0.56 for anxiety and 1.11 for depression, as measured with the BAI and BDI-II, respectively [30]. As we aim to compare the intervention with a TAU group, the results of a meta-analysis comparing CBT transdiagnostic treatments versus TAU have also been considered in the estimation of the expected sample size [106]. This meta-analysis reported a medium post-treatment effect size of 0.44 for depression and of 0.34 for anxiety between transdiagnostic treatment protocols vs. TAU conditions. The type of support we provide in this intervention (contact with researchers before, during and after the treatment period) has also been taking into account when estimating the expected sample size, as defined in a previous meta-analysis focused on Internet-based psychological treatments for depression [107]. Based on a power of .80 in a one-tailed test, an alpha of .05, and an estimated drop-out rate of around 30 % [65, 108] we need a sample size of 100 per condition to detect a post-treatment effect size of 0.40 (Cohen’s d) between both groups. Therefore, the total sample size was determined at 200.

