#### Analysis

Intention-to-treat analyses and per protocol analyses will be performed. Reporting of the results will follow CONSORT recommendations [75, 76]. First, the two groups will be compared in order to verify that there are no significant differences between them at baseline using samples t-tests for continuous distributed variables and chi-squares test of independence for categorical to confirm that they are comparable after randomization.

The intention-to-treat principle will be used when analyzing primary and secondary post-treatment data and data collected at the 3- and 12-month follow-ups using mixed effect models with full information maximum likelihood estimation. This method has been recommended for its flexibility over repeated-measures ANOVAs to handle missing date more appropriately [109].

Within and between-group changes will be computed calculating standardized effect sizes (Cohen’s d). Cohen’s d is calculated by dividing the differences between means by the pooled standard deviation [110]. An effect size of 0.20 is considered to be small, of 0.50 to be moderate, and 0.80 and above to be large [110].

Per protocol analyses (compliers only analysis) will also be conducted. Despite this procedure suffers from selection bias, it can help to draw conclusions about the maximum treatment efficacy in patients who comply fully with the treatment [111].

As the trial is still in execution, the state of the art regarding analytic methodology for RCT will be reviewed before analyzing the data, thus variations in the selection of the most appropriate analytic procedures may occur.

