Finally, a number of potential limitations should be indicated. First, dropout rates are expected to be high (around 30 %) [67, 110]. Efforts to maintain these drop-out rates below this percentage will be made by providing human support (before, during, and after the intervention) and ICT-support (for example, emails and mobile phone text messages). Second, negative attitudes towards Internet interventions by both clinicians and patients may affect recruitment as well as dropout rates. To minimize the effect of negative attitudes, the nature and characteristics of the intervention will be explained to clinicians involved in the trial. Moreover, for this purpose they will be given a handbook with relevant information about the study (for example objectives of the study, study design, and characteristics of the intervention). In order to increase participant’s credibility, prior to enrollment they will be given a sheet with relevant information concerning the characteristics and objectives of the study, and other issues related to ethics, voluntary participation and confidentiality of the data. Finally, other difficulties could be problems with recruitment, as many people who attend public mental health units do not have access to the Internet at home.

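### Two unranked primary outcomes, but alpha and power are set for one test: the stated 5% and 80% fit neither an either-scale nor a both-scales rule for success

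*Protocol article*

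**What the plan says.** The abstract's methods paragraph states that "Primary outcome measures will be the BAI and the BDI-II", and the Primary outcomes section lists the same two scales. Neither place ranks them or says whether effectiveness requires one or both.

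The Sample size section first reports an earlier trial with "between-group effect sizes of 0.56 for anxiety and 1.11 for depression, as measured with the BAI and BDI-II". It then gives a meta-analysis against treatment as usual, with 0.44 for depression and 0.34 for anxiety. From these it settles on one calculation: "Based on a power of .80 in a one-tailed test, an alpha of .05, and an estimated drop-out rate of around 30" per cent, "we need a sample size of 100 per condition to detect a post-treatment effect size of 0.40 (Cohen’s d) between both groups". The paragraph ends: "Therefore, the total sample size was determined at 200". No alpha split between the scales is mentioned.

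The Analysis section applies mixed models with full information maximum likelihood to primary and secondary outcomes, at post-treatment and at both follow-ups, under intention to treat. Per-protocol analyses are added. It closes by saying that "variations in the selection of the most appropriate analytic procedures may occur".

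**The concern.** One alpha and one power describe one test of one outcome. This trial has two primary outcomes, so those figures mean something definite only once a success rule links the two tests. Two rules are natural, and the stated figures fit neither:

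- **Either scale suffices.** Testing each at an unsplit .05 does not hold the overall error at 5%.
- **Both scales are required.** The error is held, but 80% on each scale is not 80% for the claim.

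At stake is the headline conclusion when the scales disagree. The protocol itself expects a smaller effect on anxiety than on depression, so disagreement is a realistic outcome, and nothing in the article says how it would be read.

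**Working it through.** **Inputs.** From the article: two primary outcomes; alpha .05, one-tailed; power .80; d = 0.40; 100 per arm, with 1:1 allocation; about 30% dropout, hence 100 × 0.70 = 70 evaluable per arm; cited effects of 0.34 (anxiety) and 0.44 (depression). Assumed: the correlation ρ between the two test statistics, which the article does not give, taken as 0.3 to 0.7. Normal approximations are used throughout.

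**1. The plan's own figure.** n per arm = 2(1.645 + 0.842)²/0.40² = 77.3, so 78 evaluable. Multiplying by 1.30 gives 102, close to the stated 100; dividing by 0.70 gives 112. The figure therefore reproduces as one test of one outcome at the full .05, with dropout added as a multiplier. At 70 evaluable per arm, a single scale has power Φ(0.40√35 − 1.645) = Φ(0.721) = 76.5%. That shortfall from 80% is a separate matter from the present point.

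**2. Rule: either scale suffices.** Familywise error when neither scale has an effect is 1 − Φ₂(1.645, 1.645; ρ), where Φ₂ is the bivariate normal distribution function.

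| ρ | 0 | 0.3 | 0.5 | 0.7 |
|---|---|---|---|---|
| Familywise error | 9.75% | 9.3% | 8.8% | 8.0% |

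The ρ = 0 entry is 1 − 0.95². Above ρ = 0.7 the figure keeps falling (7.5% at 0.8).

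**3. Rule: both scales required.** Power is Φ₂(δ₁ − 1.645, δ₂ − 1.645; ρ), with δ = d√(n/2).

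| Evaluable per arm, effects | Power per scale | ρ = 0.3 | ρ = 0.5 | ρ = 0.7 |
|---|---|---|---|---|
| 78, d = 0.40 on both | 80.3% | 67.1% | 69.2% | 71.7% |
| 70, d = 0.40 on both | 76.5% | 61.6% | 64.0% | 66.9% |
| 70, 0.34 and 0.44 | 64.3%, 83.1% | 56.4% | 58.6% | 61.0% |
| 100 (no information lost), d = 0.40 on both | 88.2% | 79.2% | 80.5% | 82.1% |

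The first row isolates the effect of having two outcomes, because each scale there has the planned 80%.

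**4. How often the rule would decide the conclusion.** The chance that exactly one scale is significant at 70 per arm is the sum of the two single-scale powers minus twice the joint power. For ρ from 0.3 to 0.7 this is 30% down to 19% at d = 0.40, and 35% down to 25% with the cited effects.

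**5. Cost of controlling the error.** One-sided .05 overall, 70 per arm, d = 0.40, power for at least one claim:

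| ρ | Unadjusted | Hochberg | Holm |
|---|---|---|---|
| 0.3 | 91.4% | 85.4% | 84.1% |
| 0.5 | 89.0% | 82.5% | 81.0% |
| 0.7 | 86.1% | 79.2% | 77.4% |

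**The case against.** The strongest reply is that a testing rule for two primaries is ordinary analysis-plan content, and a journal article may leave it there. This stands as far as it goes: the absence of a rule is not in itself the finding. What remains is that the article does fix alpha, power and sample size, and fixes them for a single test. A later plan could add a rule, but it would not make the published sizing statement describe that rule.

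Several stronger readings are tempting but not supported:

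- *That each scale will be tested at the full 5%.* The only alpha in the article is in the sample-size paragraph, and the Analysis section gives none. Testing each scale at .05 is an inference from an unsplit figure, so the 8-9% is conditional.
- *That the trial has both inflated error and low power.* It cannot have both. If either scale suffices, power for at least one claim exceeds 80%; if both are required, the type I error is at most 5%.
- *That the follow-ups and the per-protocol set are further routes to success.* The sizing targets a post-treatment effect, and the article itself warns of selection bias in the per-protocol analysis.
- *That the closing sentence of the Analysis section reopens the choice of outcomes.* It concerns analytic procedures, to be reviewed before the data are analysed.

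The power shortfall should not be overstated either. The figures at 70 per arm treat dropout as total loss of information, whereas the planned maximum-likelihood model, or baseline adjustment, may recover some of it. If nothing were lost, the both-scales rule would have about 79-82% power at d = 0.40. Part of the gap at 70 per arm comes from how dropout was added, not from having two outcomes.

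**Conclusion.** The point holds as a mismatch between two unranked primary outcomes and a sizing statement written for one test. Which consequence follows depends on a success rule that the article does not give:

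- under an either-scale rule at the stated alpha, familywise error of about 8-9% instead of 5%;
- under a both-scales rule, power of about 67-72% with 78 evaluable per arm, or 62-67% with 70, instead of 80%.

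Both ranges assume a correlation of 0.3 to 0.7 and one-tailed tests. The power ranges also assume d = 0.40 on both scales and no gain from the model. The matter bears on the main conclusion and should be corrected, but it does not undermine the design. The trial is still recruiting, so the rule can be fixed in time.

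**What to change.** Before any outcome is seen by arm:

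1. Define one confirmatory family: BAI and BDI-II at post-treatment (18 weeks), in the intention-to-treat mixed model.
2. Test it with Hochberg (or Holm) at the trial's overall alpha, so that either scale can be claimed with the familywise error controlled.
3. Label the 3- and 12-month results and the per-protocol results as secondary.
4. Restate the power in the Sample size section for this rule.

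The change needs no new assessments or procedures. Its price is a halved threshold when only one scale is significant. At overall one-sided .05 and 70 per arm, with d = 0.40, power for at least one claim is about 79-85% under Hochberg, against about 86-91% unadjusted.

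If the sponsor prefers to require both scales, no alpha adjustment is needed, but 80% power at d = 0.40 then takes 102 down to 95 evaluable per arm for correlations of 0.3 to 0.7. With 30% dropout that is 102/0.70 = 146 down to 95/0.70 = 136 per arm.

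Moving to a two-sided test is a separate decision with a further power cost: at 70 per arm and d = 0.40, a single scale falls from 76.5% to 65.8%. It should be made and costed on its own.

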**Discussion:**

Although the effectiveness of face-to-face transdiagnostic protocols has been investigated in previous studies, the number of published transdiagnostic Internet-based programs is still quite low. To our knowledge, this is the first randomized controlled trial studying the effectiveness of a transdiagnostic Internet-based treatment for several emotional disorders in public specialized care. Combining both a transdiagnostic approach with an Internet-based therapy format may help to decrease the burden of mental disorders, reducing the difficulties associated with disorder-specific treatments and facilitating access to people in need of treatment. Strengths and limitations are discussed.

**Trial registration:**

ClinicalTrials.gov NCT02345668. Registered 27 July 2015.

## Background

### Introduction

Emotional disorders (ED) (anxiety and mood disorders) are among the most prevalent mental disorders, with a life prevalence of 29 % and comorbidity rates ranging between 40 and 80 % [1, 2]. If the person experiencing the disorder is not adequately treated, the course often becomes chronic and can significantly affect important functioning areas such as work and social relationships [3, 4]. Moreover, the medical care costs and production losses associated with these mental health problems in Europe are huge [2]. These data strongly suggest that efficacious and efficient treatments are needed to address this important health problem [5–8]. Nevertheless, despite these alarming data, evidence exists indicating that most people with depression and anxiety disorders (less than 50 %) do not receive treatment. [9]. To reduce the burden of mental illness, some authors have emphasized the need for an approach that goes beyond the dominant face-to-face treatment approach in order to provide help to people in need of evidence-based treatments, and this approach includes the use of the media, self-help interventions, the use of special settings and information and communication technologies (ICT) [10].

Efficacious psychological treatments for ED currently exist, and a number of evidence-based cognitive-behavioral treatments (CBT) targeting specific disorders have been developed in the past 20 years [11–17]. However, disorder-specific treatment protocols have some problems. First, the high comorbidity rates among ED. Epidemiological studies have shown that at least 55 % of people suffering from depression and an anxiety disorder suffer from another anxiety disorder at the time of the assessment, and this prevalence rate increases to 76 % when different lifespan diagnoses are taken into account [18]. Consequently, clinicians often have to decide on which is the most adequate disorder-specific protocol in these cases, and because these treatments focus on disorder-specific symptomatology, other comorbid diagnoses do not receive sufficient attention [19]. Second, disorder-specific protocols frequently do not target subthreshold symptoms that did not meet diagnostic thresholds for one disorder or another but that may be important to address in the treatment [20]. Third, the high rate in which “not otherwise specified” diagnoses of clinical significance are assigned as current and lifetime conditions for which there are not specific interventions [18]. Finally, the fact that each manualized specific-disorder treatment requires the use of separate handbooks, workbooks and protocols may be an obstacle in the dissemination of evidence-treatments due to its costs and the important amount of training to become adequately familiar with each of the different treatments [20].

### Transdiagnostic approach

In recent years, there has been great interest in treatment strategies (referred to as transdiagnostic treatments) that might be more widely effective across these diverse mental health disorders. Unlike disorder-specific treatment protocols, transdiagnostic treatments generally include treatments aimed at addressing different disorders (for example, different anxiety disorders) with a single protocol [21]. A growing body of research showing the efficacy of transdiagnostic treatments for anxiety disorders [22–27], and for comorbid depression and anxiety disorders [28–30] has emerged in the past years. Moreover, the efficacy and effectiveness of transdiagnostic treatment protocols for ED have been shown in two recent meta-analyses [31, 32].

An important line of research within the transdiagnostic approach is that initiated by D. H. Barlow [20, 33–36]. Barlow’s theory of triple vulnerability emphasizes the underlying vulnerabilities that are common to emotional disorders and help to explain the comorbidity among these diverse conditions [20, 33]. From this theoretical framework, ED are regarded as minor variations in the manifestation of a broader syndrome (that is, “general neurotic syndrome”) such that the development of treatments directly targeting this underlying syndrome rather than symptom-specific variations would result in a more parsimonious, easier to disseminate treatment approach [20]. It would also result in a more inclusive approach, as it lays on the existence of biological and psychological vulnerabilities that are hypothesized to be common among anxiety disorders, unipolar mood disorders, and other disorders such as somatoform and dissociative disorders [20, 37]. Based on this perspective, Barlow’s team designed the Unified Protocol (UP) [37–41], a transdiagnostic treatment protocol that emphasizes the role of emotion regulation in understanding and treating ED. Due to difficulties in emotion regulation, people with ED often react negatively to their own emotions, and they are more likely to use maladaptive emotion regulation strategies that, in turn, increase the frequency and intensity of negative emotions [37]. To enhance adaptive emotion regulation strategies, the UP focuses on four essential aspects: increasing present-focused emotional awareness, addressing emotional avoidance, promoting cognitive flexibility, and facilitating exposure to avoided situations and sensations. The results obtained using this protocol in a traditional face-to-face format demonstrate its effectiveness and are encouraging [30, 38, 42].

The core of all emotion regulation difficulties has been pointed out to be neuroticism/behavioral inhibition (N/BI) [34, 43, 44]. Previous research supports the role of N/BI in accounting for the onset, overlap, and maintenance of ED [33, 44–46]. Literature has also highlighted the role of extraversion/behavioral activation (E/BA) in ED. For instance, structural models have indicated that low E/BA is associated with unipolar depression [47], social anxiety [48] and agoraphobia [49]. Also, a recent meta-analysis indicated that most individuals with anxiety and mood disorders show low levels of E/BA [50]. The effect of the UP on these two temperament dimensions has been demonstrated recently [51].

Literature about Dialectical Behavior Therapy (DBT) has also highlighted the role of emotion dysregulation in psychological disorders [52, 53]. A primary goal in DBT is training patients in adaptive emotion regulation strategies, as emotion dysregulation is assumed to be a key factor in the development and maintenance of these problems [52]. Emotion regulation difficulties have also been shown to be a transdiagnostic factor across a number of psychological disorders, including anxiety and depression [54–58]. A treatment protocol derived from DBT emotion regulation skills training has been tested in a recent study, suggesting that training patients in emotion regulation strategies (for example increasing emotional awareness) may help to reduce anxious and depressive symptoms among distinct ED [59].

### Internet-based treatment protocols

ICT such as the Internet may facilitate access by people for whom traditional therapy is not available [10]. Internet-based treatments have proven to be a very promising tool for solving several mental health problems and enhancing the dissemination of evidence-based treatments [60–63]. Several advantages regarding the recruitment of patients, assessment, diagnosis and case management in Internet-based treatment protocols have been indicated in a recent article [64]. A number of systematic reviews have shown that Internet-based treatments are efficacious [65–69]. Moreover, meta-analyses reveal that these protocols produce higher effect sizes compared to control groups [60, 65, 70] and that they are as efficacious as face-to-face traditional treatments [66, 70–72]. In sum, there is extensive evidence showing the efficacy of these treatments. However, the evidence available about Internet-based treatments is almost exclusively limited to disorder-specific protocols. Indeed, very few studies combining both a transdiagnostic approach and an Internet-based delivery format have been tested through randomized controlled trials (RCT) [25, 26, 29, 73]. Moreover, studies analyzing the efficacy of transdiagnostic Internet-based treatments, address the treatment of anxiety disorders only [25, 26, 73] or have used open-trial designs [28, 74]. Among those focused on anxiety and depression the existing protocols do not contemplate either the treatment of “not otherwise specified” diagnoses or obsessive-compulsive disorder [29], or target a small range of ED [29]. Moreover, to our knowledge, no RCT have been carried out on the effectiveness of a transdiagnostic Internet-based protocol versus treatment as usual (TAU) in public mental specialized care settings.

